### Assessments

Assessment will take place at baseline (prior to treatment randomization), and at 3 and 12 months following baseline assessment. Socio-demographic information (age, sex, ethnicity, employment status and living situation) will be collected at baseline only, but all other measures will be administered at all 3 time points.

#### Illicit drug use

An instant result urine toxicology test screening for metabolites of opiates will provide an objective measure of illicit drug use. This will be supplemented by an interview using sections of the Maudsley Addiction Profile (MAP) [33]. Section B records the number of days that the participant has used heroin, cocaine, benzodiazepines and alcohol in the past 28 days, and the average amount of use of each drug on a using day. Section C captures the number of days that the participant has injected drugs in the past 28 days [33]. Section E records the number of days of paid work and the amount of acquisitive crime committed in past 28 days [33]. In addition, the Leeds Dependence Questionnaire [34] will serve as a diagnostic measure of the severity of dependence and as a treatment outcome measure that works with abstinent patients. It consists of 10 questions that are summed to compute a maximum score of 30, with a higher score denoting more severe dependence.

#### Psychological and Social Functioning

The Clinical Outcome in Routine Evaluation scale [35] is a 34-item self-complete questionnaire that gives a measure of psychological morbidity across four domains: (a) well-being (4 items); (b) symptoms (12 items - depression × 4, anxiety × 4, trauma × 2, physical × 2); (c) functioning (12 items - general × 4, social × 4, and close × 4); and risk (6 items - to self × 4 or to others × 2). The Social Satisfaction Questionnaire [36] measures change in social problems. It is an eight-item self-complete questionnaire with a maximum score of 24, where higher scores represent greater satisfaction with housing, finances, and relationships.

#### Motivation to Change Behaviour

The Readiness to Change Questionnaire - Treatment Version [37] is a 15-item questionnaire, based on Prochaska and DiClemente’s stages of change model [38], that assigns drug users to Precontemplation, Contemplation, and Action stages.

#### Social Network Composition and Support

The Important People Drug and Alcohol Interview [14] is a researcher-administered adaption of the Important People and Activities measure that incorporates questions about substance abuse. Respondents are asked to provide the first name and relationship of up to 10 members of their social network who have been important to them in the last 3 months. For each network member identified, the respondent rates frequency of contact, how important the person is to them, the extent to which the person was generally supportive of them, substance use status, frequency of substance use, how this person has reacted to their substance use, and how this person has felt about them coming for treatment. The Interpersonal Support Evaluation List [39] consists of a list of 40 statements concerning the perceived availability of potential social resources. Items each fall into four 10-item subscales: tangible support, appraisal support, self-esteem support, belonging support. Each is scored between 0 and 30, with a higher score indicating greater support.

#### Therapeutic engagement

The Engagement section of the Client Evaluation of Self and Treatment [40] is a 36-item self-completion questionnaire. Each item is scored between 1 and 5, yielding four sub-scale scores representing treatment participation, treatment satisfaction, counseling rapport, and peer support.

#### Family member assessment

Each participant recruited into the trial will be asked to nominate a family member to be approached to take part in a short telephone interview at baseline, 3 and 12 months. Symptoms of stress experienced by the family member, coping behaviors used and the impact of the addiction problem on the family member will be assessed using a validated set of standardized questionnaire measures [41]. The Family Member Impact scale is a 16-item questionnaire designed to assess the extent of harmful impact that a family member perceives the relative’s drinking or drug-taking to have on them or the whole family over the previous 3-month period. Response options for each individual item (‘not at all’, ‘once or twice’, ‘sometimes’ and ‘often’) are scored 0, 1, 2 and 3, respectively. The Symptom Rating Test measures physical and psychological ill health in the general population. It is brief and easy to complete. Respondents are asked to indicate whether they have experienced each of 30 symptoms in the past 3 months using response options ‘never’, ‘sometimes’ or ‘often’ (scored 0, 1 and 2, respectively). The Coping Questionnaire measures 30 coping actions over the previous 3-month period. Respondents are given four response options for each item: ‘no’, ‘once or twice’, ‘sometimes’ and ‘often’, scored 0, 1, 2 and 3, respectively. Previous research suggests the presence of three factors (tolerant, engaged and withdrawal coping). Each factor is scored separately as a sub-scale and a total score is calculated by adding the three factor scores.

#### Qualitative assessment

A small number of participants randomized to receive B-SBNT (n = 10), family members of patients receiving B-SBNT (n = 10) and therapists trained in B-SBNT (n = 6) will be asked to participate in a short semi-structured qualitative interview with the aim of establishing the level of satisfaction with the treatment, the perceived process of change and the helpful aspects of the therapeutic process. In the case of therapists, the interviews will also assess how B-SBNT differs from standard treatment.

#### Economic evaluation

The economic evaluation will be conducted from a societal perspective, incorporating the widest measurement of costs and outcomes as possible. The base-case analysis will estimate the incremental cost-effectiveness of B-SBNT versus the two other treatment conditions using the primary outcome of abstinence of heroin. Further analyses will incorporate additional outcomes measured from the perspective of the patients and network members and will include assessment of ‘capability wellbeing’ as measured by the Investigating Choice Experiments Capability measure for Adults (ICECAP-A) [42] and health status as measured by the EQ-5D [43] at baseline, 3 months and 12 months. Health service and criminal justice service resource use will be measured using the Client Service Receipt Inventory [44], and will include number of general practitioner visits, outpatient and inpatient visits, community care and drug-related services, criminal justice service costs and medication use. Unit costs will be obtained from standard sources.

### Sample size

As this is an early phase study, a formal sample size calculation is not appropriate. A total of 120 participants will be recruited to the trial (n = 40 per treatment condition). If the proportion of patients that stop taking heroin in the B-SBNT group is 0.3 we can then produce an approximate 95% confidence interval of 0.18 to 0.44 for this estimate; if the proportion is found to be 0.1, an approximate 95% confidence interval will be 0.01 to 0.19, showing reasonable precision.

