### Staff recruitment and training

This study aims to test the feasibility of training NHS staff to deliver a social network intervention. Therefore, clinical staff will be asked to volunteer to participate in the study with no attempt made to randomly select therapists. A minimum of two clinicians per treatment condition is required at each project site, but more staff will be trained if available. Training will follow the format adopted in previous pilot work in this area [23]. Each active intervention will be delivered according to a purpose-designed treatment manual. The treatment manual for B-SBNT will be based on a manual from previous research [23] adapted for a four-session format. The PGS intervention will follow the manual developed as part of the National Treatment Agency *Routes to Recovery* initiative [27]. There will be an initial 1 day training session to introduce staff to the key concepts and procedures involved in each treatment intervention, and all staff in the B-SBNT condition will be required to pilot the methods with one clinical case prior to the commencement of the trial. The trial will only commence once it has been established that B-SBNT is being delivered with sufficient fidelity, and supervision will be provided for both active treatment conditions on a monthly basis.

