### Data analysis

#### Trial outcome analysis

Data will be analyzed according to the intention-to-treat principle; all randomized participants will be included in the analysis irrespective of whether or not they stayed in the trial, with missing data treated as failing to achieve reduction. The primary outcome measure will be the number of days in the preceding 4 weeks that the participant has used heroin. The primary analyses will compare B-SBNT with PGS and TAU, and subjects will be analyzed using a generalized mixed model, including experimental group as an explanatory classification variable. The therapists will be included as random effects [45]. In supportive analyses we will examine sequential measurements of heroin use over 28-day periods as repeated measures, using appropriate error structures, including a measure of patient adherence to randomized therapy over time. Analysis of continuous secondary outcomes will be conducted using analogous statistical models, including changes in level of drug-related problems (such as injecting drug use, criminal activity, and psychological symptoms), severity of drug dependence, motivation for drug abstinence, level of social satisfaction, and level of therapeutic engagement. A further important research outcome will be changes in social network structure and function, and level of general social support. The major analyses will be pre-specified in a statistical analysis plan completed prior to database lock. Analyses will be conducted in SAS 9.2 or above (SAS Institute Inc., Cary, NC, USA; http://www.sas.com/software/sas9; accessed 11/07/13)

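### Minor error: the 95% confidence interval given for a proportion of 0.3 with 40 patients should start at 0.16, not 0.18, by the method that gives the second interval

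*Protocol article*

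**What the plan says.** The Sample size section declines a power calculation: "As this is an early phase study, a formal sample size calculation is not appropriate". It then fixes the numbers: "A total of 120 participants will be recruited to the trial (n = 40 per treatment condition"). In place of power it offers two illustrations of how well the proportion stopping heroin in the B-SBNT arm would be estimated. At an observed proportion of 0.3, "we can then produce an approximate 95% confidence interval of 0.18 to 0.44 for this estimate". At 0.1, "an approximate 95% confidence interval will be 0.01 to 0.19, showing reasonable precision". The method behind the intervals is not named, and no intraclass correlation or design effect is mentioned.

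Two other sections bear on the optional remark about clustering. Trial outcome analysis puts therapists in the primary model as random effects. Staff recruitment and training says "A minimum of two clinicians per treatment condition is required at each project site", and adds that more will be trained if they are available.

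**The concern.** The two intervals stand side by side and share the same n, so one would expect one formula to give both. The first is not symmetric about 0.3: its lower limit lies 0.12 below and its upper limit 0.14 above. A Wald interval is symmetric at any n, so the first interval cannot be Wald, yet the second is symmetric about 0.1 and looks like a Wald interval.

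The stake is modest. These two intervals are the only quantitative support for 40 per arm, and the error makes the precision look slightly better than it is. The Discussion says the trial should show whether a definitive trial is realistic in size, so its own statement of precision ought to be right.

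**Working it through.** **Inputs.** n = 40 in the B-SBNT arm, proportions 0.3 (12/40) and 0.1 (4/40), and 95% confidence, all from Sample size. Take z = 1.96. Missing outcomes do not reduce n, because Trial outcome analysis keeps every randomized patient and counts missing data as failure.

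**Step 1: reproduce the second interval.** Wald: p ± z·√(p(1 − p)/n).
0.1 ± 1.96·√(0.1 × 0.9/40) = 0.1 ± 1.96 × 0.0474 = 0.1 ± 0.093, so 0.007 to 0.193. Rounded, this is 0.01 to 0.19, as stated.

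**Step 2: apply the same formula to the first.**
0.3 ± 1.96·√(0.3 × 0.7/40) = 0.3 ± 1.96 × 0.0725 = 0.3 ± 0.142, so 0.158 to 0.442. Rounded, this is 0.16 to 0.44. The upper limit agrees with the article and the lower does not. Width: 0.442 − 0.158 = 0.284, against 0.44 − 0.18 = 0.26 as stated.

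**Step 3: try other methods at n = 40.**

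| Method | 12/40 | 4/40 |
|---|---|---|
| Article | 0.18 to 0.44 | 0.01 to 0.19 |
| Wald | 0.158 to 0.442 | 0.007 to 0.193 |
| Wilson | 0.181 to 0.454 | 0.040 to 0.231 |
| Agresti-Coull | 0.180 to 0.455 | 0.034 to 0.236 |
| Clopper-Pearson | 0.166 to 0.465 | 0.028 to 0.237 |
| Jeffreys | 0.176 to 0.452 | 0.035 to 0.220 |
| Mid-P | 0.174 to 0.454 | 0.033 to 0.224 |
| Likelihood ratio | 0.173 to 0.451 | 0.032 to 0.217 |
| Logit | 0.179 to 0.457 | 0.038 to 0.238 |
| Arcsine | 0.170 to 0.449 | 0.028 to 0.211 |

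No row gives 0.18 to 0.44. The 95% methods whose lower limit rounds to 0.18 have an upper limit of at least 0.45. A 90% Wald interval, 0.181 to 0.419, does not fit either. The stated pair can be reached at other sample sizes and proportions, for example 15/48 by Wald (0.181 to 0.444), but not at n = 40. A slip for 0.16, or a Wilson-type lower limit set beside a Wald upper limit, would explain it; the article does not show which.

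**Step 4: what independence is worth (optional remark).** The limits that reproduce are plain binomial figures, so no design effect is in them. With k therapists sharing 40 patients equally, m = 40/k and the variance is multiplied by 1 + (m − 1)·ICC. The article gives no ICC, so the values here are assumptions. Wald intervals at 0.3:

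- Four therapists (two at each of two sites, the minimum), m = 10. ICC 0.05: 1 + 9 × 0.05 = 1.45; half-width 0.142 × √1.45 = 0.171; interval 0.13 to 0.47.
- Six therapists, m = 6.67. ICC 0.05: 1 + 5.67 × 0.05 = 1.283; half-width 0.142 × √1.283 = 0.161; interval 0.14 to 0.46.
- Four therapists, ICC 0.01: factor 1.09; interval 0.15 to 0.45, with a half-width about 4% larger than without clustering.
- Four therapists, ICC 0.10: factor 1.90; interval 0.10 to 0.50.

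**The case against.** The best defence is that little depends on the figure. The article calls the intervals approximate and says a formal calculation is out of place; 40 per arm was not solved from them, and no test or decision uses them. A width of 0.28 supports the article's favourable description of the precision about as well as 0.26 does. All of this stands and limits the point to a minor one. It does not make the lower limit right: the other three limits agree with one formula to two decimals, and a difference of 0.02 is more than rounding.

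A reader might go further in two ways, and the article supports neither.

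First, that the interval at 0.1 is also wrong. It is a correct Wald interval, labelled approximate. With four events a Wilson interval is preferable, but it mostly shifts the range upward: its width is 0.231 − 0.040 = 0.191, against 0.186 for Wald. The move of the upper limit from 0.19 to 0.23 is not by itself evidence of worse precision, since the lower limit rises too.

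Second, that therapist clustering makes the stated precision wrong by a known amount, or contradicts the analysis. The therapist random effects belong to a model for days of heroin use, while the intervals illustrate a proportion in one arm. Four therapists is a minimum; the article allows more, and Qualitative assessment plans interviews with six B-SBNT therapists. The size of the effect depends on an ICC that the article does not give. That the intervals assume independence is a fair remark, but no more than that.

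**Conclusion.** The first interval is wrong as printed. By the method that gives the second interval, it should read 0.16 to 0.44, with a width of 0.28 and not 0.26. This rests only on n = 40, the stated proportion and 95% confidence, and no standard method rescues the printed pair. The error is minor: it affects one limit, by 0.02, in the direction that flatters precision.

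It does not follow that 40 per arm is inadequate, that the second interval is in error, or that the true precision is worse by any particular amount because of clustering. The figures for clustering hold only under the assumed ICC, the assumed number of therapists and equal caseloads.

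**What to change.** In Sample size, do one of the following:

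- replace 0.18 with 0.16, so that both intervals are Wald (0.16 to 0.44 and 0.01 to 0.19); or
- recompute both by one better method and name it, for example Wilson: 0.18 to 0.45 and 0.04 to 0.23.

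Leave the sample size as it is.

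Optionally, add a sentence saying that the intervals treat patients as independent although the primary model has therapist random effects. If a clustered interval is shown, use the same method as for the others and label the ICC and number of therapists as assumptions. With Wald and an assumed ICC of 0.05, it is about 0.13 to 0.47 with four therapists and 0.14 to 0.46 with six. These should not be set beside Wilson figures: Wilson on the effective sample size for four therapists (40/1.45 = 27.6) gives about 0.16 to 0.49.

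The cost is one to three numbers in one paragraph and a slightly less favourable statement of precision. Nothing in the design or analysis changes.

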### Data analysis

#### Trial outcome analysis

Data will be analyzed according to the intention-to-treat principle; all randomized participants will be included in the analysis irrespective of whether or not they stayed in the trial, with missing data treated as failing to achieve reduction. The primary outcome measure will be the number of days in the preceding 4 weeks that the participant has used heroin. The primary analyses will compare B-SBNT with PGS and TAU, and subjects will be analyzed using a generalized mixed model, including experimental group as an explanatory classification variable. The therapists will be included as random effects [45]. In supportive analyses we will examine sequential measurements of heroin use over 28-day periods as repeated measures, using appropriate error structures, including a measure of patient adherence to randomized therapy over time. Analysis of continuous secondary outcomes will be conducted using analogous statistical models, including changes in level of drug-related problems (such as injecting drug use, criminal activity, and psychological symptoms), severity of drug dependence, motivation for drug abstinence, level of social satisfaction, and level of therapeutic engagement. A further important research outcome will be changes in social network structure and function, and level of general social support. The major analyses will be pre-specified in a statistical analysis plan completed prior to database lock. Analyses will be conducted in SAS 9.2 or above (SAS Institute Inc., Cary, NC, USA; http://www.sas.com/software/sas9; accessed 11/07/13)

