#### Brief Social Behavior and Network Therapy

Participants randomized to receive B-SBNT will be offered four 50-minute B-SBNT sessions over a maximum of 6 weeks. The treatment manual will combine the most effective components of the SBNT intervention from earlier studies [24] with elements of node-link mapping to facilitate the training and delivery of the intervention. The treatment will involve working with the patient to draw a ‘network diagram’ during the first session to identify potential social support for change that could be drawn upon during the remaining sessions. Following this, potential supportive network members identified by the participant will be approached and invited to take part in treatment sessions to enhance the social support for change in drug use. The therapist will use elements of communication skill development, coping behaviors and the development of joint activities to support the process, with the ultimate aim of building a network-supported relapse management plan.

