#### Treatment as usual

Participants randomized to receive TAU will continue to receive usual care with no additional therapy sessions. The participating treatment services do not specify a particular therapeutic style for working with patients, and clinicians do not follow a treatment manual. They are encouraged to use a variety of techniques, and some will have been exposed to the goal setting and SBNT techniques as part of their continuing professional development. Our research group conducted one of the few published studies describing routine treatment in OST services in Birmingham [29]. Meetings with patients occurred between weekly and fortnightly, and lasted an average of 45 minutes. Session activities fell into four broad categories, each delivered in similar amounts: case management, signposting of other services, structured psychosocial interventions, and other activities (for example, medication issues). We therefore anticipate that TAU will consist of interventions that are both less structured and less frequent than the two active treatments under test.

Prior to the commencement of the trial the elements that comprise ‘standard treatment’ in drug services at both project sites will be evaluated based on the methodology of previous research [29]. Ten clinical cases will be selected at random from each site. Electronic data will be screened for the preceding 6-week period to determine the quantity and frequency of drug treatment sessions. Short unstructured interviews will then be conducted with each key-worker to identify the content of each treatment session.

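### The supportive repeated-measures model appears to include post-randomisation adherence, which has no defined value in TAU, so its active-versus-TAU effects need not estimate the randomised effect

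*Protocol article*

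**What the plan says.** All of the analysis text is in the protocol article, Data analysis, Trial outcome analysis.

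- **Primary analysis.** The outcome is a count of days: "The primary outcome measure will be the number of days in the preceding 4 weeks that the participant has used heroin". The population is all randomised: "Data will be analyzed according to the intention-to-treat principle; all randomized participants will be included in the analysis". The model is given as "subjects will be analyzed using a generalized mixed model, including experimental group as an explanatory classification variable", with therapists as random effects. No adherence term is mentioned.
- **Supportive analysis.** "In supportive analyses we will examine sequential measurements of heroin use over 28-day periods as repeated measures", with suitable error structures, "including a measure of patient adherence to randomized therapy over time".
- **Active arms.** B-SBNT offers "four 50-minute B-SBNT sessions over a maximum of 6 weeks" (Brief Social Behavior and Network Therapy). PGS offers the same number and length of sessions and is there to match intensity (Personal Goal Setting).
- **TAU.** "Participants randomized to receive TAU will continue to receive usual care with no additional therapy sessions". The services "do not specify a particular therapeutic style for working with patients, and clinicians do not follow a treatment manual" (Treatment as usual). No measure of adherence is defined for this arm.

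**The concern.** Sessions attended are observed after allocation. Patients who are doing better may attend more, and attendance may be part of how therapy works. In either case, conditioning on attendance gives up the protection of randomisation.

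TAU adds a second difficulty. Adherence to added therapy does not vary there, because there is none. Its coefficient is then learned from the active arms alone, and the TAU contrast depends on whatever value TAU patients are given.

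An analysis called supportive will be read as corroborating the primary result. The Discussion makes an encouraging signal on the main outcome a condition for moving to a definitive trial. A supportive model that can hide or enlarge a real difference from TAU could mislead that decision.

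**Working it through.** The protocol states no figure on this point, so there is nothing to reproduce. The check is of the mechanism and its plausible size.

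**Step 1: what the wording implies.** In the primary-model sentence, the word 'including' introduces a model term (experimental group). In the supportive sentence it follows the error structures and introduces adherence. A model term is the natural reading, though how it enters is not spelled out.

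**Step 2: the algebra.** Take one follow-up and least squares with group and sessions attended, A. Give every TAU patient the value c. A does not vary within TAU, so its slope b comes only from the active arms. For active arm k:

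group coefficient = (mean Y in arm k - mean Y in TAU) - b x (mean A in arm k - c)

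The first bracket is the randomised contrast. The rest is a shift:
- c = 0: shift = -b x mean A
- c = 4: shift = +b x (4 - mean A)

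If better prognosis goes with more attendance, b is negative, so the two codings shift the estimate in opposite directions. Between B-SBNT and PGS the value c cancels, leaving -b x (difference in mean A). In this linear form that is zero when mean attendance is equal.

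**Step 3: first simulation.** From the protocol: 40 per arm and 4 sessions offered. Assumed: prognosis worth -3 days per SD, residual SD 6 days, a logistic model for attendance with prognosis slope 0, 0.5 or 1, and 3,000 replicates. Estimates are B-SBNT minus TAU, in days.

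| Attendance-prognosis slope | True effect | Without adherence | TAU coded 0 | TAU coded 4 |
|---|---|---|---|---|
| 0 | 0 | 0.0 | 0.0 | 0.0 |
| 0.5 | 0 | 0.0 | +2.85 | -2.10 |
| 1 | 0 | 0.0 | +3.68 | -2.85 |
| 0.5 | -3 | -3.0 | -0.2 | -5.1 |
| 1 | -3 | -3.0 | +0.7 | -5.9 |
| 0 | -1 per B-SBNT session | -2.3 | -1.1 | -3.1 |

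The last row shows distortion with no prognostic link, because the effect runs through the sessions.

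Check against Step 2: the two codings should differ by -4b. At slope 0.5, 2.85 + 2.10 = 4.95, so b = -1.24 and mean A = 2.85/1.24 = 2.3. At slope 1, 3.68 + 2.85 = 6.53, so b = -1.63 and mean A = 3.68/1.63, again about 2.3. The results follow the formula.

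B-SBNT minus PGS stayed at its true value throughout (0.0, -3.0 and -2.3). Attendance was simulated with the same distribution and prognostic link in both active arms.

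**Step 4: second simulation, varying the strength of the link.** Assumed: null effect, outcome SD 9 days, about 2.5 sessions attended on average, TAU coded 0.

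| Latent correlation, prognosis and attendance | Bias (days) |
|---|---|
| 0 | 0.0 |
| 0.1 | +1.4 |
| 0.2 | +3.2 |
| 0.3 | +4.5 |
| 0.4 | +6.3 |

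At 0.3 the slope is -1.8 per session, and 1.8 x 2.5 = 4.5, as the formula says. Slightly different ways of generating attendance at the same correlation give up to +4.9. If prognosis explains only half the outcome variance, the bias falls to +3.2. If baseline is also adjusted for and captures half of prognosis, it falls to +1.6.

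**Step 5: comparison with sampling error.** At SD 9, the 95% half-width of a two-arm contrast is 1.96 x 9 x sqrt(2/40) = 3.9 days. The bias exceeds it at correlations of 0.3 and 0.4, but not at 0.2 or below, nor in the two milder variants.

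**The case against.** The strongest reply is that the text never says adherence is adjusted for. An interaction, a dose-response analysis within the active arms, or a causal method would also fit the words, and nothing says the group coefficient of this model will be read as the treatment effect. The SAP, which is not shown, is to pre-specify the major analyses. The analysis is only supportive, in a pilot for which attendance is a legitimate feasibility question. TAU patients also see key-workers (weekly to fortnightly in the earlier study of routine care that the protocol describes), so some attendance could be counted for them.

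Much of this stands as a limit on the point. It does not remove it. The inclusion of adherence is stated, so this is not merely a detail left to the SAP. Key-worker attendance is a different variable from attendance at an added, manualised therapy, and the protocol does not define it as the measure.

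Three stronger readings are tempting and unsupported:
- **The whole supportive model is biased and uninterpretable.** B-SBNT and PGS share one attendance scale, and their contrast is biased only if attendance, or its link to prognosis, differs between them.
- **The model will make the active arms look harmful.** That holds only with TAU coded 0. Coded as fully adherent, the same null makes them look beneficial. The protocol fixes neither coding.
- **The trial's main result is compromised.** No adherence term is mentioned for the primary intention-to-treat model.

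**Conclusion.** The point holds in a limited form. On the natural reading, the active-versus-TAU group effects from the supportive repeated-measures model do not estimate the randomised effect if attendance shares causes with heroin use or carries part of the treatment effect. Both are plausible here, but neither is established by the protocol.

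The size is uncertain. Apart from the 40 per arm and the four sessions, the simulation inputs are assumptions, and the simulations use a single follow-up and least squares instead of the full mixed model. A single figure such as +4.9 days should not be quoted as the expected bias. The sign is not determined until the TAU value is chosen.

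**What to change.** In the Trial outcome analysis section and the SAP:

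1. Fit and report the supportive repeated-measures group effects without adherence in the model.
2. Put any adherence analysis in a separate paragraph and label it exploratory. Define the measure, and either confine it to the two active arms or state how TAU is handled.
3. Optionally, if the effect of actually receiving therapy is wanted, specify a complier-average estimand with randomisation as the instrument, separately for B-SBNT versus TAU and PGS versus TAU. This would be imprecise with 40 per arm and is not needed to resolve the point.

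The cost is a few lines of text and at most one extra model. Attendance at intervention appointments is already among the feasibility measures in the Discussion, so no new data are needed.
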